#### Youth leadership facilitators

Research from other settings in India suggests potential benefits of combining peer-facilitated interventions with complementary activities [18], and that developing adolescents’ self-efficacy and psychosocial resilience is a ‘missing piece’ in improving girls’ health [7]. Our formative research also indicated that adolescents would like opportunities to participate in cultural and sports activities in their communities. On this basis, the community youth team involves a youth leadership facilitator to deliver fun activities that build adolescents’ confidence and help to keep them engaged in the PLA cycle. These activities are also an opportunity to provide information related to adolescent health and development, and to reach out to the rest of the community. Activities are open to all girls and boys in the community and occur every 2 months. They run in parallel with the PLA cycle and include football tournaments and other sports activities, problem management sessions, cycling sessions and nature walks. Youth leadership facilitators are local adults recruited by Ekjut on the basis of their leadership skills, experience of working with young people, and understanding of the principles of PLA. Facilitators participate in monthly meetings with *yuva saathis*, coordinators and supervisors in order to coordinate and plan intervention activities.

#### Livelihood promoters

Through our formative research, adolescents and their parents informed us that they wanted opportunities to participate in livelihood training to develop practical skills related to farming and environmental management. We therefore engaged livelihood promoters, who are adults recruited for their skills and knowledge in farming practices and environmental management, to deliver a programme of livelihood promotion activities. Activities reflect the seasons, are selected in consultation with communities and include paddy cultivation, multi-cropping, compost-making and other organic farming techniques, tree planting, rainwater harvesting, and revival of farmers and save the forest groups (*van samitiy*). Activities will run approximately every 3 months in both intervention and control arms and are family-focused, involving both adolescents and their parents. The programme has three main aims: (1) to provide adolescents with practical skills that they can use in later life; (2) to improve food security for families, which will help to improve dietary diversity; and (3) to provide a common benefit to both intervention and control arms to help build support for the research across the trial arms.

### Trial timeline and status

The baseline survey was conducted between June 2016 and January 2017. In April and May 2017, we recruited and trained the community youth teams. The intervention will be implemented over 36 months from June 2017 to May 2020. The endline survey will partially overlap with intervention implementation and will be conducted between December 2019 and April 2020. A time frame for the research activities is shown in Fig. 2.

**Fig. 2 Fig2:**
[figure not shown]
Study timeline

### Research questions

We seek to test the effects of the intervention on three main outcomes: school attendance, dietary diversity and mental health. We chose these to represent the broad range of health and development issues affecting adolescent girls in India and because formative research indicated that these are important problems for girls in the study area.

#### Primary research questions

What is the effect of an intervention comprising participatory adolescent groups, youth leadership activities and livelihood promotion, delivered by a community youth team, on adolescent girls’ school attendance, dietary diversity and mental health?

#### Secondary research questions

Secondary research questions explore intermediate effects of the intervention on the pathway to impact on school attendance, dietary diversity and mental health. We ask, does the intervention:
increase the uptake of school-related entitlements (e.g., cash, bicycles, books, mid-day meals for girls in upper primary, scholarships)?reduce the number of girls who were absent from school in the past 2 weeks?increase adolescent girls’ decision-making ability, self-efficacy and resilience?reduce the percentage of girls who drank alcohol in the past month?increase the percentage of girls with attitudes supportive of equitable gender norms related to education and domestic work?reduce exposure to emotional and physical violence and increase the number of girls who intervene to reduce emotional and physical violence against their peers?

### Study outcomes

The trial has three primary outcomes: school attendance, dietary diversity and mental health problems (Table 2). We will assess the percentage of girls attending school or college at the time of the endline survey. Information on school attendance will be self-reported, and we will cross-check answers in school registers for 10% of girls randomly selected from the sample. We will use the Food and Nutrition Technical Assistance tool to measure mean dietary diversity score (based on 24-h recall) [19]. For mental health problems, we will compare the mean score on the Brief Problem Monitor–Youth (BPM-Y) across trial arms [20]. The BPM-Y includes items on internalising (depression and anxiety), externalising (conduct disorder and oppositional defiant disorder) and attention problems. Secondary outcomes on the pathway to change for the primary outcomes are outlined in Table 2 and presented in the theory of change. Tertiary outcomes are also shown in the theory of change (Additional files 1 and 3) and relate to further hypothesised outcomes of the intervention that are not directly related to the primary outcomes. Additional file 3 also outlines how each outcome is measured and if baseline data are available.

**Table 2 Tab2:** Trial outcomes

Primary outcomes	
1	Percentage of adolescent girls attending school or college
2	Mean dietary diversity score, based on 24-h recall
3	Mean score on the Brief Problem Monitor–Youth
Secondary outcomes	
1	Percentage of girls making decisions independently and with others about the food they eat, including how much they eat and what types of food they eat
2	Mean score on gender role attitudes index
3	Percentage of girls making decisions independently and with others about friends, spending money and purchases
4	Mean score on the Schwarzer General Self-Efficacy (GSE) Scale
5	Mean score on the Child and Youth Resilience Measure 11-item version (CYRM-B)
6	Percentage of girls who report experiencing emotional violence in the past 12 months
7	Percentage of girls who report experiencing physical violence in the past 12 months
8	Percentage of girls who report intervening to reduce emotional violence against their peers in the past 12 months
9	Percentage of girls who report intervening to reduce physical violence against their peers in the past 12 months
10	Percentage of girls who report being absent from school in the past 2 weeks
11	Percentage of girls accessing at least one school-related entitlement (cash, bicycles, books, midday meal scheme)
12	Percentage of girls who drank alcohol in the past month
Tertiary outcomes	
1	Percentage of girls who took at least four iron and folic acid supplements in the past month
2	Percentage of girls aged 15–19 and all married girls who have correct knowledge about the contraceptive pill, condoms and the IUD
3	Percentage of girls who use sanitary napkins or clean cloths during their period
4	Percentage of girls aged 15–19 and all married girls who know that abortion is legal
5	Percentage of girls who have received take home rations in the past month
6	Percentage of girls underweight (less than −2 SD median BMI for age and sex)
7	Percentage of girls stunted (less than −2 SD median height for age and sex)
8	Mean MUAC score

*BMI* body mass index, *IUD* intra-uterine device, *MUAC* Mid Upper Arm Circumference

### Sample size and power

The size of the study area, and hence the number of clusters, was chosen for logistical reasons. With a district-level crude birth rate of around 23 per 1000 population and accounting for child deaths, we expected to find an estimated 8800 adolescents aged 10–19 (4400 girls) in our proposed intervention area. We anticipated that in each cluster there would be ~115 adolescent girls aged 10–19 years.

A total of 3324 adolescent girls aged 10–19 years participated in the baseline survey: 82% of an estimated 4068 girls in the 38 clusters. The mean number of girls in each cluster was 87 (SD, 29.9). We aim to interview the same number of girls in the endline survey. With a mean cluster size of 87, a coefficient of variation of cluster sizes of 0.3 [29], and using intra-cluster correlation coefficients (ICCs) from our baseline data, the trial will have 80% power to detect a nine-percentage-point increase in the proportion of girls attending school or college (ICC, 0.03), from a baseline prevalence of 69% to 78%; a 0.9-point increase in mean dietary diversity score (ICC, 0.40), from a mean baseline score of 3.4 (SD, 1.4) to 4.3; and a 2.7-point decrease in BPM-Y score (ICC, 0.39) from a mean baseline score of 6.0 (SD, 4.3) to 3.4. The significance level is set at 0.05. We performed these calculations in Stata software (version 14; StataCorp, College Station, TX, USA). We anticipate that including baseline data in our analysis will lead to gains in power but do not attempt to quantify these here.

### Data collection, cleaning and storage

In this section, we describe data collection processes for the endline survey. These are identical to processes followed at baseline, which are described elsewhere [21]. Twelve monitors who are independent from the community youth teams will undertake data collection. In each of the study clusters, they will visit all households in order to identify eligible adolescent girls. In households with an eligible girl, monitors will explain the study to the girl and seek her consent. For girls under the age of 18, monitors will also seek consent from the girl’s caregiver. The monitor will then find a convenient time to conduct an interview with the girl in her home (e.g., outside school hours for school-going girls). If girls are not available when the monitor visits the household, the reason for unavailability will be recorded. Through these interviews, we will collect data relating to the primary and secondary outcomes, as well as data on the socio-economic status of the household and for the process evaluation. Data will be collected using mobile phones programmed using the CommCare data collection platform, which uses automated skip patterns and in-built checking and consistency logic to support data validation. Data will be downloaded from the server every 2 weeks. We will check the number of interviews completed and look for any problems. Every month, we will check the data for outliers, errors and missing data using automated do-files in Stata. The final dataset will be stored on a password-protected hard drive after removing individual identifying information.

### Blinding

Data collection during the endline survey will overlap with intervention activities by approximately 3 months. Monitors will not be given information about the allocation of clusters. However, through their monitoring activities in the villages, they may encounter some of the intervention activities or meet members of the community youth teams. Because of the participatory nature of the intervention, adolescents and the community youth teams cannot be blind to allocation. The researcher conducting the final trial analyses will be blind to allocation. Analyses for the primary outcomes will be repeated by an independent statistician also blind to allocation.

### Analysis plans

Primary analysis will employ an intention-to-treat approach, including all adolescent girls aged 10–19 living in the study area, regardless of their level of participation in the intervention activities. We have three primary outcomes. We think that success in improving at least one of these outcomes could help inform decisions about future scale-up. We will declare the trial a success if we find a significant (two-tailed *P* < 0.05) benefit for at least one outcome in conjunction with a collectively ‘positive signal’ for the other two outcomes. A ‘positive signal’ is defined as at least one of the two outcomes in the direction of benefit, neither outcome showing significant harm, and if for one outcome the direction of effect is towards benefit and for the other it is towards harm, then we require the (two-tailed test) *P* value for the former outcome to be smaller than that for the latter. The type I error rate corresponding to this definition of success varies according to the correlations between the three outcomes, which we expect to be positive. Under perfect positive correlations, the type I error rate is 5%. Under independence and the null hypothesis (no intervention effect on any outcome), the probability of observing success in conjunction with one, two or three significant benefits observed for individual outcomes is 3.38% (3 × 0.025 × 0.95^2^ × 0.5), 0.18% (3 × 0.025^2^ × 0.95) and 0.00% (0.025^3^), respectively. Consequently, the overall probability is 3.56%, and the type I error rate assuming a symmetric definition of overall trial failure (harm) is 7.12%. For primary and secondary outcomes, we will conduct cross-sectional analyses to compare differences between the control and intervention arms of the trial, using regression models with generalised estimating equations (GEEs) to adjust for clustering and model baseline and endline information together. We will use the exchangeable working correlation structure. To assess the effect of the intervention, our regression models will include an indicator of time (endline vs. baseline) and an indicator of intervention, coded 1 for participants measured at endline in the intervention arm and 0 otherwise. This analysis approach has been termed a ‘constrained baseline analysis’ [30]. Our baseline data show that dietary diversity is slightly positively skewed and BPM-Y scores are very positively skewed. We will model mean dietary diversity scores using linear regression. We will model BPM-Y scores using linear regression after transformation by the function log(1 + *x*), noting that our analytic approach (marginal model fitted by GEE) provides robustness by avoiding distributional assumptions. We will use a logistic regression model to test for a difference in the percentage of girls attending school between arms as a binary outcome. We will adjust for the same set of pre-specified prognostic factors (asset quintile, tribal status and age) and for strata for each outcome. We will additionally adjust for further socio-economic factors, should the data monitoring committee note important imbalances between arms among baseline participants. However, because there could be collinearity between such factors or between such factors and the pre-specified prognostic factors, it may be that not all can be included or that some may need to combined. The final model will be selected without reference to intervention effect (i.e., without seeing the impact of different potential models on the intervention effect estimate). We do not plan to conduct any sensitivity analysis for the effects of missing data, because the refusal rate for the endline survey is expected to be low (< 1%), in line with the baseline survey. We think that short-term cross-over between intervention and control areas is likely to be rare, because the main reason for moving is to attend boarding school, and there are few boarding schools in our study clusters. We will be able to identify participants who have crossed over through their exposure to the intervention and will provide an estimate of ‘contamination’, though we expect this to be less than 1% of participants.

We plan to carry out two sub-group analyses for the primary outcomes. The first will assess the effects of the intervention on the primary outcomes by age, categorising girls as younger (10–14 years) or older (15–19 years). The second will examine intervention effects on the primary outcomes by household wealth quintile. For sub-groups of age and wealth quintile, the intervention effects will be presented within each sub-group following the same approach as in the main analyses. Formal testing for a difference in intervention effect across sub-groups will be based on testing interaction terms. Tertiary outcomes that are present in the theory of change will be reported in the process evaluation as exploratory analyses.

We will convene a data monitoring committee in 2019 and 2020 to (1) examine the comparability of trial arms and potentially identify socio-economic variables that differ between arms to adjust for in the final analysis, (2) approve our data analysis plan and ensure we conduct the final analyses in accordance with this, and (3) provide recommendations on the interpretation of results and additional analyses.

The anonymised trial dataset with data on primary and secondary outcomes and code used in the main analyses will be made available as supplementary files with the main trial publication.

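### The success rule's type I error is quoted only at independence (7.12%) and perfect correlation (5%), but almost every positive correlation in between gives a higher value, up to about 11.7–11.8%

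*Protocol article*

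**What the plan says.** All of this is in the protocol article, under Analysis plans. The section states "We have three primary outcomes" and sets the decision rule: "We will declare the trial a success if we find a significant (two-tailed *P* < 0.05) benefit for at least one outcome", together with a positive signal on the remaining two. That signal requires "at least one of the two outcomes in the direction of benefit, neither outcome showing significant harm". If the two point in opposite directions, "then we require the (two-tailed test) *P* value for the former outcome to be smaller than that for the latter".

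On the error rate, the section says that it "varies according to the correlations between the three outcomes, which we expect to be positive". Two values follow. The first is "Under perfect positive correlations, the type I error rate is 5" (per cent). The second is for independence under the global null, built from three terms for one, two or three significant benefits: "Consequently, the overall probability is 3.56%, and the type I error rate assuming a symmetric definition of overall trial failure (harm) is 7.12" (per cent). No value is given for any correlation between 0 and 1, and no size is given for the correlations expected.

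**The concern.** The case the authors expect, positive but imperfect correlation, lies between the two points they quote. A reader shown 7.12% at one end and 5% at the other will naturally take the truth to lie between them. That would be right only if the error fell steadily as correlation rose, and it does not.

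Positive correlation acts on the rule in two opposite ways:

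- It lowers the chance that at least one outcome is falsely significant. This lowers the error.
- Once one outcome is falsely significant, it pulls the other two in the same direction, so the positive-signal condition is met more often. This raises the error.

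If the second effect dominates at first, the safeguard filters least well where the authors expect to be, and both quoted figures understate the error. At stake is the stated false-positive rate of the rule that decides whether the trial is called a success, which the section links to decisions about scale-up.

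**Working it through.** **Inputs** (all from Analysis plans): three outcomes; two-sided 0.05 for each, so 0.025 in the direction of benefit with critical value 1.96; the positive-signal condition as written. With z statistics scored so that positive means benefit, the mixed-direction P-value comparison is equivalent to z_a + z_b > 0 for the two remaining outcomes.

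**Assumption:** the document gives no correlation size, so a common correlation ρ of the three test statistics is scanned from 0 to 1, with some unequal sets.

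**Step 1: the plan's own figure at independence.**

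- One significant benefit: 3 × 0.025 × 0.95² × 0.5 = 0.03384
- Two: 3 × 0.025² × 0.95 = 0.00178
- Three: 0.025³ = 0.00002
- Sum: 0.03564, or 3.56%. Doubled for the mirror-image harm rule: 7.13%. The printed 7.12% is twice the rounded 3.56%.

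Doubling is legitimate because success excludes any significant harm, so the two events cannot both occur.

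**Step 2: the plan's figure at ρ = 1.** The three statistics coincide, so the rule reduces to one two-sided test at 5% (2.5% for success). This also agrees.

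**Step 3: values in between.** The rule was coded in full and applied to millions of simulated null trivariate normal statistics at each ρ. The code returns 3.56%, 7.1% and 5.0% at the two endpoints, so it implements the same definition.

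| ρ | False success | Both directions | At least one false benefit, no signal required |
|---|---|---|---|
| 0 | 3.56% | 7.1% | 7.3% |
| 0.1 | 4.4% | 8.8% | 7.2% |
| 0.2 | 5.0% | 10.1% | 7.0% |
| 0.3 | 5.5% | 11.0% | 6.8% |
| 0.5 | 5.9% | 11.7–11.8% | 6.3% |
| 0.7 | 5.4% | 10.8–10.9% | 5.5% |
| 0.8 | 4.9% | 9.8% | 4.9% |
| 0.9 | 4.2% | 8.4% | 4.2% |
| 0.95 | 3.7% | 7.3% | 3.7% |
| 1 | 2.5% | 5.0% | 2.5% |

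The ranges reflect simulation error between runs. The two-direction error is about 7.2% at ρ = 0.955 and 7.1% at 0.96, so it crosses the quoted 7.12% there.

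**Step 4: the mechanism.** Dividing the second column by the fourth gives the share of false benefits that the positive-signal condition lets through:

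- ρ = 0: 3.56/7.31 = 0.49
- ρ = 0.3: 5.5/6.8 = 0.81
- ρ = 0.5: 5.9/6.3 = 0.94
- ρ = 0.8: practically 1

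The chance of any false benefit falls only from 7.3% to 6.3% between ρ = 0 and 0.5, while the share let through almost doubles.

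**Step 5: unequal correlations.** Positive sets between 0 and 0.8 (at least one above 0) gave 8.3% to 11.6%; the set (0.1, 0.3, 0.5) gave 10.8%. The result does not depend on the correlations being equal.

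**The case against.** No stated figure is wrong. Each percentage is labelled with its condition, both reproduce, and the section says openly that the rate varies. It never calls the two values a range and does not claim control at 5%. All of this stands: the fault is an incomplete account of how the rule behaves, not a miscalculation.

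A reader might infer that the trial will run at about 12%, or at more than twice 5%, in the setting its authors expect. The document does not support that. It gives the sign of the correlations but not their size, and schooling, a 24-hour dietary recall and a mental health score are different enough that small correlations cannot be excluded. At ρ = 0.05 the error is 8.0%, and at 0.15 about 9.5%. It is at least double 5% only for ρ from about 0.2 to 0.78.

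Half of the two-direction rate is false declaration of harm, under a mirror-image rule that the section introduces only for this calculation. The comparison with 7.12% is like for like, but the chance of wrongly declaring success never exceeds about 5.9%.

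A reader might also infer that the P threshold must be lowered. The authors disclose a rate above 5% and explain why success on one outcome is useful to them. That is a design judgement which the arithmetic does not overturn.

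A fuller analysis plan may show more. That would not change the error statement printed here, which is what needs correcting.

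**Conclusion.** The point holds as a correction to the stated error rate. The figures 7.12% and 5% are right at independence and perfect correlation, but they do not bound the error. For any common correlation of the test statistics from just above 0 to about 0.955, the two-direction rate exceeds the larger quoted figure, with a maximum of about 11.7–11.8% near 0.5. False success rises from 3.56% to at most about 5.9%, against 2.5% for a single outcome.

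This rests on approximately normal test statistics, all three outcomes null, and correlation measured between test statistics scored in the direction of benefit (lower is better for the Brief Problem Monitor–Youth). The direction of the result needs only imperfect positive correlation, short of about 0.955. The exact rate depends on a size that the document does not give. Outcome-specific estimates and P values are unaffected; only the overall success label and its quoted error are.

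**What to change.** Rewrite the error statement along these lines: the type I error is 7.1% under independence (3.6% for false success), rises to a maximum of about 11.8% (5.9%) near a common correlation of 0.5, and is 5% (2.5%) only under perfect correlation. This costs nothing beyond wording and can be done when the data monitoring committee approves the data analysis plan.

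Preferably, also report the value at the correlations estimated from the baseline survey, which has all three outcomes in the 38 clusters. Correlations of cluster means from 38 clusters are imprecise: the standard error on Fisher's z scale is 1/√35 = 0.17, so an estimate of 0.3 has a 95% interval of roughly −0.02 to 0.57. The estimate should therefore sit beside the maximum and not replace it.

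Optional, for the team to weigh: tighten the per-outcome threshold. Two-sided P < 0.0285 keeps the worst case at about 7.1%, with detectable differences about 9% larger (t quantiles, 36 degrees of freedom, 80% power). P < 0.0195 keeps it at about 5%, with detectable differences about 14% larger, and is conservative elsewhere (2.9% at independence). With the number of clusters fixed for logistical reasons, that loss could not be recovered by adding clusters, so accepting the higher rate openly is also defensible.

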### Randomisation

We conducted the randomisation on the 22nd of February 2017, allocating 19 clusters to the intervention arm and 19 to the control arm. Clusters were stratified on the basis of five strata: (1) clusters with a secondary school and an adolescent club (clubs are community-based health and development groups for adolescents run by the Integrated Development Foundation), (2) clusters with a secondary school and no adolescent clubs, (3) clusters without a secondary school but with an adolescent club, (4) clusters without a secondary school and without an adolescent club, and (5) clusters having a population of more than 1500. Figure 1 describes the study profile. To ensure transparency of the randomisation process, we invited participants from the local community (village headmen, community health workers and a local government representative) to participate in the randomisation. We explained the intervention and the purpose of randomisation to the participants. Clusters were numbered and displayed on a wall. Identical balls were numbered 1 to 38, representing each of the 38 clusters. For each of the five strata, participants placed the numbered balls corresponding to the clusters in that strata into a local tombola device. They operated the machine and sequentially allocated each ball to the intervention and control arms. Allocation was not concealed to participants present during the randomisation.

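### One exchangeable correlation across both surveys makes the expected power gain from baseline data depend on a between-survey cluster correlation that the protocol does not give

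*Protocol article*

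**What the plan says.** In the Protocol article, Analysis plans, the primary and secondary outcomes are analysed by GEE "to adjust for clustering and model baseline and endline information together". The treatment term is "an indicator of intervention, coded 1 for participants measured at endline in the intervention arm and 0 otherwise", alongside a time indicator, so no arm difference is allowed at baseline. The working correlation is fixed in one sentence: "We will use the exchangeable working correlation structure". No separate between-survey correlation is named.

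Sample size and power treats the trial as an endline comparison, with ICCs taken from the baseline data: 0.03 for school attendance, 0.40 for dietary diversity and 0.39 for BPM-Y. It then adds: "We anticipate that including baseline data in our analysis will lead to gains in power but do not attempt to quantify these here". No correlation of cluster levels between the two surveys is given anywhere.

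**The concern.** Each cluster contributes girls from two cross-sectional surveys, run from June 2016 to January 2017 and from December 2019 to April 2020 (Trial timeline and status). One exchangeable parameter sets the working correlation between two girls in different surveys equal to that between two girls in the same survey. In effect it assumes a CAC of 1: a cluster's departure from the overall mean at baseline is carried over in full to endline.

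If the true CAC is well below 1, the model corrects too much for chance baseline differences and adds noise to the treatment estimate. When the ICC is high the weight on baseline is close to 1 and hardly responds to the data. The stake is precision. Readers will take the endline-only 80% power as a floor, with the baseline data adding to it. Under the stated analysis it is a floor only if the CAC is high enough.

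**Working it through.** **Inputs.** Randomisation: "allocating 19 clusters to the intervention arm and 19 to the control arm". Sample size and power: "With a mean cluster size of 87, a coefficient of variation of cluster sizes of 0.3"; "We aim to interview the same number of girls in the endline survey", so m = 87 in each survey; ICCs as above; effects and SDs of 0.9 (SD 1.4) for diet, 2.7 (SD 4.3) for BPM-Y, and 69% to 78% for school attendance; two-sided 5%. The CAC is not given and is varied from 0 to 1. Further assumptions: equal survey sizes, no covariates, a linear approximation for the logistic outcome, and the raw-scale ICC for BPM-Y (the ICC of log(1+x) is not given).

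**The plan's own figures.** Design effect = 1 + ((1 + CV²)m − 1) × ICC. For diet: 1 + (1.09 × 87 − 1) × 0.40 = 38.5. Effective n per arm = 19 × 87 / 38.5 = 42.9. SE = 1.4 × √(2/42.9) = 0.302. The difference detectable with 80% power is 0.85 (normal) to 0.87 (t with 36 df). The same steps give 2.57 to 2.64 for BPM-Y and 8.4 to 8.6 percentage points for school attendance. These agree with the stated figures after rounding. At the rounded effects, endline-only power by t(36) is 83% (diet), 82% (BPM-Y) and 84% (school).

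**Weight on baseline.** With equal survey sizes the constrained baseline estimate is (endline difference) − b × (baseline difference), where
- a ≈ ICC × (1 + CAC)/2 is the single correlation fitted to the pooled data;
- b = m·a / (1 + (m − 1)·a).

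**Variance relative to endline-only.** The correlation of a cluster's two survey means is R = CAC × m·ICC / (1 + (m − 1)·ICC). The planned analysis has ratio 1 + b² − 2bR. A weight matched to the true correlation has ratio 1 − R².

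Example, diet at CAC 0.3: a = 0.40 × 1.3/2 = 0.26; b = 22.62/23.36 = 0.968; R = 0.3 × 34.8/35.4 = 0.295; ratio = 1 + 0.937 − 0.571 = 1.37. The SE becomes 0.302 × √1.37 = 0.353, and power 70%.

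| Assumed CAC | Diet b | Diet ratio, planned | Diet ratio, matched | Diet power, planned | Diet power, matched | School b | School ratio, planned |
|---|---|---|---|---|---|---|---|
| 0 | 0.96 | 1.91 | 1.00 | 55% | 83% | 0.57 | 1.32 |
| 0.2 | 0.96 | 1.55 | 0.96 | 64% | 84% | 0.61 | 1.20 |
| 0.3 | 0.97 | 1.37 | 0.91 | 70% | 86% | 0.63 | 1.12 |
| 0.5 | 0.97 | 0.99 | 0.76 | 83% | 91% | 0.67 | 0.96 |
| 0.8 | 0.98 | 0.42 | 0.38 | 99% | >99% | 0.71 | 0.68 |

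Power is by t(36). BPM-Y ratios match diet to within 0.01.

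**Break-even.** The planned analysis gains only when R > b/2. This gives a CAC of 0.495 for diet, 0.495 for BPM-Y and 0.45 for school attendance. If covariates cut the residual ICC to 0.1-0.2, b is still 0.82-0.96 and the break-even CAC 0.48-0.49.

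**Unequal clusters.** Simulating 38 clusters of unequal size (1,200 runs per setting) gave ratios of 2.05, 1.53, 1.16 and 0.72 at CAC 0, 0.3, 0.5 and 0.7 for ICC 0.40, and 1.46, 1.17, 1.03 and 0.76 for ICC 0.03. Other simulations for ICC 0.40 gave 1.54-1.61 at CAC 0.3 and 1.05 at 0.5. The formula is therefore somewhat favourable to the plan at low CAC, and break-even with unequal clusters lies nearer 0.50-0.55.

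**The case against.** The strongest reply is that the harm rests on a figure the document does not contain. By the formula, planned power falls below 80% only if the CAC is under about 0.46 (diet), 0.47 (BPM-Y) or 0.33 (school attendance). At 0.8 the planned model does far better than endline-only. The same villages are surveyed twice by the same procedures, which favours persistence. This stands: a loss of power is possible, not shown.

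A reader might infer a low CAC from the change of girls, the 24-hour recall or the different survey months. The document does not support that inference. Turnover of girls and recall noise are mainly individual variation, already counted outside the ICC and averaged over 87 girls. A seasonal shift common to all clusters is absorbed by the time indicator. Only shifts specific to a cluster within a survey lower the CAC.

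A reader might also infer that the whole analysis becomes a change-score comparison. That is close to true for diet and BPM-Y, but not for school attendance, where the weight is 0.57-0.73.

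Finally, the 80% power uses no baseline gain, and the protocol declines to put a number on that gain. True, but the gain is still expected without condition, and the stated analysis can turn it into a loss.

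**Conclusion.** The point holds as one about efficiency. For two of the three primary outcomes the stated working correlation fixes the baseline weight at about 0.96-0.98 regardless of the true CAC. The planned analysis then beats ignoring baseline only above a CAC of roughly 0.45-0.55. Across assumed CACs of 0.2 to 0.8, diet power runs from about 64% to 99%, against 83% endline-only. For school attendance the worst-case variance ratio is about 1.3 by formula (1.46 simulated with unequal clusters).

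It does not follow that the trial will miss its stated power, since the CAC is unknown. Nor is the estimate biased: robust standard errors keep the test roughly valid. The figures rest on the assumptions listed with the inputs, of which the raw-scale ICC for BPM-Y is the least certain. The case for change is that a matched weighting never has more variance than endline-only in this calculation, and still does better than the plan at CAC 0.5 (ratio 0.76 against 0.99).

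**What to change.** Under Analysis plans, keep the marginal GEE and do one of the following:

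1. Replace the single exchangeable structure with a working correlation that has separate within-survey and between-survey terms.
2. Fit the GEE to endline data, with the cluster's baseline mean (or proportion) of the same outcome as a covariate beside the planned ones.

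Do not move to cluster random effects for school attendance. That would change the marginal odds ratio to a cluster-conditional one and give up the robustness for which the protocol chose a marginal model.

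Under Sample size and power, say that any gain from baseline data depends on the between-survey cluster correlation.

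The cost is a change of text and code and one extra parameter. In simulation the baseline-mean covariate had about 3% more variance than endline-only at zero CAC. Its ratios were 0.95, 0.78 and 0.55 at CAC 0.3, 0.5 and 0.7. The data analysis plan was still to be approved by the data monitoring committee, so the change could be made there, before the endline effect is seen.
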